## Abstract

**Background:**

Malnutrition is an independent risk factor of postoperative morbidity and mortality and it’s observed in 20 to 50% of surgical patients. Preoperative interventions to optimize the nutritional status, reduce postoperative complications and enteral nutrition has proven to be superior to the parenteral one. Moreover, regardless of the nutritional status of the patient, surgery impairs the immunological response, thus increasing the risk of postoperative sepsis. Immunonutrition has been developed to improve the immunometabolic host response in perioperative period and it has been proven to reduce significantly postoperative infectious complications and length of hospital stay in patients undergoing elective gastrointestinal surgery for tumors. We hypothesize that a preoperative oral immunonutrition (ORAL IMPACT®) can reduce postoperative morbidity in liver resection for cancer.

**Methods/design:**

Prospective multicenter randomized placebo-controlled double-blind phase IV trial with two parallel treatment groups receiving either study product (ORAL IMPACT®) or control supplement (isocaloric isonitrogenous supplement - IMPACT CONTROL®) for 7 days before liver resection for cancer. A total of 400 patients will be enrolled. Patients will be stratified according to the type of hepatectomy, the presence of chronic liver disease and the investigator center. The main end-point is to evaluate in intention-to-treat analysis the overall 30-day morbidity. Secondary end-points are to assess the 30-day infectious and non-infectious morbidity, length of antibiotic treatment and hospital stay, modifications on total food intake, compliance to treatment, side-effects of immunonutrition, impact on liver regeneration and sarcopenia, and to perform a medico-economic analysis.

**Discussion:**

The overall morbidity rate after liver resection is 22% to 42%. Infectious post-operative complications (12% to 23%) increase the length of hospital stay and costs and are responsible for a quarter of 30-day mortality. Various methods have been advocated to decrease the rate of postoperative complications but there is no evidence to support or refute the use of any treatment and further trials are required. The effects of preoperative oral immunonutrition in non-cirrhotic patients undergoing liver resection for cancer are unknown. The present trial is designed to evaluate whether the administration of a short-term preoperative oral immunonutrition can reduce postoperative morbidity in non-cirrhotic patients undergoing liver resection for cancer.

**Trial registration:**

Clinicaltrial.gov: NCT02041871.

## Background

Hepatic resection is the treatment of choice for selected patients with benign and malignant hepatobiliary disease. Malignant tumors represent about 63 to 90% of whole liver surgery [1, 2] and the most common diagnosis is metastatic colorectal cancer [3, 4]. Primary hepatic and biliary cancers account for about 20% of liver resection, of which hepatocellular carcinoma (HCC) is the most common [1]. Only in 13 to 30% of hepatectomies an underlying liver disease, such as cirrhosis, is present. Over the past decade, many large series have documented an improvement in perioperative results, with operative mortality rates after liver resection typically less than 5% in high-volume centers. Actually liver resections are associated with about 3.5% risk of 30-days mortality [5]. The overall morbidity rate, reported in different series, is from 22 to 42% of which 10% to 15% are major post-operative complications resulting in a prolongation of hospital stay [1, 6, 7]. The most common complications are bile leak, post-operative infections, liver failure, renal failure, cardio-vascular complications and hemorrhage. About 12% to 23% of patients undergoing liver resection develop infectious complications including chest and urinary tract infections, wound infections and infected abdominal collections [6, 8]. The infectious complications account for approximately a quarter of 30-day mortality.

The negative impact of postoperative complications (POC), and specially infectious complications, on long-term outcomes after liver surgery has been widely reported for colorectal liver metastases (CLM) as well as for HCC [7, 9–12]. Various methods have been advocated to decrease the rate of infectious postoperative complications after liver resections. These include systemic interventions such as antibiotics in peri-operative period [8, 13], topical interventions such as povidone iodine gel at the time of wound closure [14] and methods to improve general health and the immunity of the individual such as prebiotics and probiotics [15, 16] and the recombinant bactericidal-permeability increasing protein in peri-operative period [17]. A recent meta-analysis of the Cochrane collaboration [18] has selected 7 randomized clinical trials from more than 1800 records identified in the literature, to determine benefits and harms of the different interventions in decreasing the infectious complications and improving the outcomes after liver resections. In any of the compared interventions there was no significant difference between the two groups in terms of mortality, numbers of serious adverse events and intensive therapy unit stay. Author’s conclusion is that till now there is no evidence to support or refute the use of any treatment and further trials are required.

To date, the effects of preoperative oral immunonutrition (ORAL IMPACT®) in non-cirrhotic patients undergoing liver resection for cancer are unknown. As seen in major gastrointestinal surgery, this treatment could significantly reduce postoperative infectious complications, length of hospital stay and care costs [19–22]. Therefore the present trial is designed to evaluate whether the administration of a short-term preoperative oral immunonutrition can reduce postoperative morbidity in non-cirrhotic patients undergoing liver resection for cancer.

## Methods/design

### Protocol overview

The PROPILS trial is a prospective multicenter randomized placebo-controlled double-blind phase IV trial with two parallel treatment groups receiving either study product (ORAL IMPACT®) or control supplement (isocaloric isonitrogenous supplement - IMPACT CONTROL®) for 7 days before liver resection for cancer. Patients will be stratified according to the type of hepatectomy (major or minor hepatectomy), the presence of a chronic liver disease and the investigator center. The main end-point is to determine in intention-to-treat analysis, the impact of immunonutrition on the overall morbidity within 30 postoperative days. Secondary end-points will be the impact of immunonutrition on postoperative 30-day infectious and non-infectious morbidity, length of antibiotic treatment, length of hospital and ICU stay, modifications on total food intake, compliance to treatment and side-effects of immunonutrition, impact on liver regeneration and sarcopenia. At last, an ancillary study will be performed to evaluate whether the supplementary costs associated to preoperative immunonutrition could be counterbalanced by its impact in care-costs.

This study is planned for a 32-month duration with a 30-month inclusion period and is registered on clinicaltrial.gov website (NCT02041871).

### Inclusion criteria

PROPILS will include adult patients undergoing planned elective liver resection for malignant tumors. The inclusion criteria are as follows: 1) liver resection for malignancies 2) including at least 1 segment resected or 3 wedge resections 3) for patients who are over 18 years of age 4) and provide a signed written consent form (Table 1).

**Table 1 Tab1:** **Selection criteria of study population**

Inclusion criteria:	- Patient older than 18 years old
	- Planned elective liver resection for malignant tumour
	- At least 1 segment resected or 3 wedge resections
Exclusion criteria:	- Patient younger than 18 years old
	- Liver resection for benign lesion
	- Liver resection associated with biliary tract surgery
	- Liver resection associated with gastro-intestinal surgery
	- Cirrhosis, defined by transient elastography or by liver biopsy
	- Renal failure defined by hemodialysis
	- Pregnancy
	- History of hypersensitivity to arginine, omega-3 fatty acids, or nucleotides
	- Inability to take oral nutrition
	- Mental condition rendering the subject unable to understand the nature, end-points and consequences of the trial

### Exclusion criteria

All patients who do not meet all the inclusion criteria will be excluded. The other exclusion criteria include liver surgery associated with biliary surgery or gastro-intestinal surgery, liver cirrhosis, defined by transient elastography (Fibroscan) or by liver biopsy, renal failure defined by hemodialysis, pregnancy, history of hypersensitivity to arginine, omega-3 fatty acids, or nucleotide, inability to take oral nutrition and mental condition rendering the subject unable to understand the nature, end-points and consequences of the trial (Table 1).

### Endpoints of trial

The primary endpoint of this trial will be the rate of overall complications classified in grade II-III-IV or V according to Dindo-Clavien classification [23] in the first 30 postoperative days (POD).

The secondary endpoints include: i)The rate of infectious complications classified in grade II, III, IV or V according to Dindo-Clavien classification in the first 30 PODs including: – Wound infection defined as any redness/ tenderness of surgical wound with discharge of pus– Abdominal abscess defined as deep collection of pus– Pulmonary tract infection characterized by abnormal chest X-ray with fever (>38°C) and WBC > 12.000 cells/mm^3^ and positive sputum or bronco-alveolar lavage.– Urinary tract infection defined as more than 10^7^ microorganisms per mL of urine– Bacteremia determined by two consecutive positive blood cultures without shock– Septic shock defined as positive blood cultures with circulatory insufficiencyii)The length of antibiotics treatment (in days)iii)The rate of non-infectious complications classified in grade II, III, IV or V according to Dindo-Clavien classification in the first 30 PODs including: – Postoperative biliary leak defined by the International Study Group of Liver Surgery (ISGLS) [24] as a bilirubin concentration in the drain fluid at least 3 times the serum bilirubin concentration on or after postoperative day 3 or as the need for radiologic or operative intervention resulting from biliary collection or bile peritonitis– Post-operative liver failure defined according the’ 50-50 criteria’ [25]: PT < 50% and total bilirubin >50 μmol/ml at POD 5.– Postoperative bleeding defined as the necessity of blood transfusion (*X*2 units) [26]– Respiratory failure characterized by the presence of dyspnea and respiratory rate >35/min or PaO2 < 70 mmHg– Circulatory insufficiency determined by unstable blood pressure requiring use of extra fluids and/or cardiac stimulants– Renal dysfunction defined by increase of serum urea and/or creatinine level (50% above baseline)– Renal failure defined as the necessity of hemodialysis– Multiple Organ Dysfunction Syndrome (MODS) characterized as a state of physiological derangement in which organ function is not capable of maintaining homeostasis– Wound dehiscence defined as any dehiscence of the fascia longer than 3 cmiv)The length of hospital and ICU stay (in days)v)Post-operative liver regeneration: all patients will undergo 4 successive volumetric helical computed tomography estimations of their liver volumes before surgery (day 0) then at POD2 (day 16), POD10 (day 24) and POD30 (day 44). Preoperative measurement of the future remnant liver will be performed using as landmarks hepatic vascular structures, identified by bolus injection of contrast, and the gallbladder. Post-operative measurements will be performed for the whole remnant liver and could be realized without injection of contrast. A volumetric assessment at POD 2 has been considered necessary to clearly estimate the volume of remnant liver. Liver regeneration at POD 10 (LR10) and 30 (LR30) are calculated by using the following formula, after assuming that the density of liver was close to 1:
vi)Sarcopenia: all patients will undergo 2 helical computed tomography estimations of psoas muscle area at the level of L3-L4 before surgery (day 0) then at POD30 (day 44).vii)Estimation of modifications on total food intake, compliance to immunonutrition treatment and side effects of immunonutrition. During treatment period, patients will be asked to fill in a formulary with an evaluation of food intake per day.

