**Liver function assessment**												
PT, INR		x		x		x		x	x	x	x	x
AST, ALT		x		x		x		x	x	x	x	x
GGT, PAL		x		x		x		x	x	x	x	x
Total and direct bilirubin		x		x		x		x	x	x	x	x
Platelets		x		x		x		x	x	x	x	x
Volumetric assessment of (future) remnant liver	x						x				x	x

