### Statistical methods

#### Sample size calculation

The hypothesis of this phase IV trial is that immunonutrition will reduce overall postoperative 30-day morbidity rate. The sample size calculation is based on the detection of significant difference in the primary end-point parameter of the trial. We assumed a postoperative complication rate of 36% in the conventional group (Arm B) according with several studies about complication rate after liver surgery. A reduction of 33.3% would be considered to indicate the efficacy of treatment. With an expected complication rate of 24% in the immunonutrition group (Arm A), the sample size necessary for the trial with a power of 80% and a one-sided significance level of 0.05 was calculated to be 180 patients per group. An assumed 10% drop-out rate in this trial (due to non-compliance, intolerance, etc.) will raise the sample size to 198 patients per group. Therefore, at least a total of 400 patients (200×2) have to be included to the trial.

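### The bilirubin cut-off for post-operative liver failure is given per millilitre, 1,000 times the presumably intended value, so the liver-failure component cannot be met as written

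*Protocol article*

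**What the plan says.** The Protocol article, Endpoints of trial, sets the third secondary endpoint as "The rate of non-infectious complications classified in grade II, III, IV or V according to Dindo-Clavien classification in the first 30 PODs including" a list of nine conditions. One of them is liver failure. The text reads "Post-operative liver failure defined according the" 50-50 criteria, cites a reference, and then spells the rule out as "PT < 50% and total bilirubin >50 μmol/ml at POD 5".

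No other part of the article restates the cut-off, gives a unit for bilirubin or corrects this one. Table 3, under Liver function assessment, schedules "Total and direct bilirubin" and prothrombin time on several days, POD 5 among them, without units.

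The primary endpoint in the same section is "the rate of overall complications classified in grade II-III-IV or V according to Dindo-Clavien classification" over the first 30 postoperative days. It does not mention the bilirubin cut-off.

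**The concern.** A threshold that decides whether a patient is a case must be attainable. Read literally, this one is not: the volume unit makes the required concentration far higher than serum can carry. The prothrombin condition cannot compensate, because the two conditions are joined by "and" in the sense of requiring both.

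At stake is the liver-failure component of a secondary endpoint in a liver-resection trial. The Background section counts liver failure among the most common complications after hepatectomy, so the component is of real interest. If the rule were programmed or applied as printed, the component would be zero in both arms and the comparison on it would carry no information.

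**Working it through.** **Inputs**

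- Cut-off as printed: more than 50 μmol/ml, together with PT below 50%, at POD 5 (Endpoints of trial).
- Presumed intended cut-off: 50 μmol/L. This is inferred from the name of the criterion, which supplies the number 50 but no unit. The cited source is not at hand.
- Molar mass of bilirubin: about 585 g/mol (584.66 used). This is an assumption, as it is not in the article.
- Highest serum bilirubin in severe liver failure: assumed anywhere from 300 to 1,500 μmol/L. The article gives no range.

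**Step 1: convert the printed unit**

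50 μmol/ml × 1,000 ml/L = 50,000 μmol/L.

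Ratio to the presumed cut-off: 50,000 / 50 = 1,000.

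**Step 2: express both as mass concentration**

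- As printed: 50,000 × 10⁻⁶ mol/L × 584.66 g/mol = 29.2 g/L, or about 2,923 mg/dL.
- Read per litre: 50 × 10⁻⁶ mol/L × 584.66 g/mol = 0.0292 g/L, or about 2.9 mg/dL.

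**Step 3: compare with attainable values**

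| Assumed highest serum bilirubin (μmol/L) | Printed cut-off divided by that value |
|---|---|
| 300 | 167 |
| 500 | 100 |
| 1,000 | 50 |
| 1,500 | 33 |

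Across the whole assumed range the printed cut-off is 33 to 167 times too high. That it cannot be reached therefore does not depend on a precise physiological ceiling. With both conditions required, the literal count for this component is 0 of the 400 planned patients.

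**Step 4: does the error reach the sample size?**

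The Sample size calculation section states: "We assumed a postoperative complication rate of 36% in the conventional group (Arm B") and "With an expected complication rate of 24% in the immunonutrition group (Arm A"), "with a power of 80% and a one-sided significance level of 0.05 was calculated to be 180 patients per group".

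The pooled two-proportion formula without continuity correction is

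n = [z₀.₉₅ √(2 p̄(1 − p̄)) + z₀.₈₀ √(p₁(1 − p₁) + p₂(1 − p₂))]² / (p₁ − p₂)²,

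with p₁ = 0.36, p₂ = 0.24 and p̄ = 0.30:

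n = [1.645 × √0.42 + 0.842 × √0.4128]² / 0.12² = (1.066 + 0.541)² / 0.0144 ≈ 179.3, rounded up to 180 per group.

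The stated figure reproduces, with power of 80.1% at 180 per group. Its inputs are overall complication rates. The bilirubin cut-off appears nowhere in it, so correcting the unit leaves 180 per group and 400 in total unchanged.

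**The case against.** The strongest reply is that this is an obvious slip of ml for L. The sentence names its criterion and cites a source, the number 50 agrees with the name, and anyone applying the printed unit would soon see that no laboratory value comes near it. The article also condenses a fuller protocol, so the slip may exist only in print. All of this is plausible and lowers the weight of the point. It does not make the printed definition usable: the article chose to state the rule, stated it wrongly and corrects it nowhere.

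Three stronger readings are tempting, and the article does not support them.

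- *Liver failure drops out of non-infectious morbidity.* A reader might infer this from a component that is always zero. But that endpoint covers non-infectious complications of grade II to V and introduces its list as included items, without saying that the list is exhaustive. Data collection and follow up has all complications recorded and graded by Dindo-Clavien. A patient treated for liver failure could still be counted, and other listed items, such as multiple organ dysfunction or circulatory insufficiency, might capture the same patient. What is surely lost under a literal reading is the liver-failure label, not necessarily the event.
- *Centres will apply different thresholds.* Six centres take part, but the article shows no competing threshold and no variation between sites. This is speculation.
- *The cut-off is 1,000 times a reachable level.* The factor of 1,000 is relative to the presumably intended cut-off. Against the highest attainable values the excess is 33 to 167 times on the assumed range.

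It is also inferred, not stated, that liver failure is computed from the Table 3 laboratory values. The POD 5 schedule for both tests makes it likely.

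**Conclusion.** The definition is wrong as written. The bilirubin condition equals 50,000 μmol/L, 1,000 times the presumably intended cut-off, and applied literally the liver-failure component of the third secondary endpoint would be zero in both arms.

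The size is minor to moderate. One of nine listed items under a secondary endpoint is affected. The primary endpoint is graded by Dindo-Clavien without reference to this cut-off, and the sample size does not depend on it. The point should not be read as a threat to the main comparison.

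The conclusion that no patient could qualify rests on the unit conversion and on the assumed ceiling of 300 to 1,500 μmol/L for serum bilirubin. The replacement unit of μmol/L is a strong inference from the name of the criterion, still to be confirmed against the cited source.

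**What to change.** Reconcile the unit of the bilirubin threshold in the liver-failure definition with the cited 50-50 criteria, presumably μmol/L, and issue the correction in the protocol and, if the slip is only there, in the article. Confirm that the eCRF field for bilirubin and the derivation of the liver-failure component use that same unit. Because the article reports that data collection is under way, make this check before the database is frozen and the blind is broken.

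The cost is one corrected unit and one check of the eCRF and the derivation. The sample size, the visit schedule and the primary analysis stay as they are.

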**Preoperative protein-energy malnutrition**												
Height	x											
Actual weight	x			x							x	x
BMI	x			x							x	x
Usual weight	x											
% of loss of weight in one and 6 months	x											
Albumin, prealbumin		x		x								
MNA-SF (for patients > 70 years old)	x											
Sarcopenia (Psoas area on CT scan)		x					x				x	x

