**Schema depicting the workflow of the study.**

Concerning the radiological investigations performed preoperatively and then on POD2, POD10 and POD30, the assessment of remnant liver volumes and of sarcopenia, will be performed by a single radiologist.

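### Psoas area is defined on two CT scans but scheduled on four, and baseline liver volumetry is given two different days: reconcile both, and adjust the POD30 psoas comparison for baseline

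*Protocol article*

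**What the plan says.** **Psoas area.** Item vi under Endpoints of trial reads "all patients will undergo 2 helical computed tomography estimations of psoas muscle area at the level of L3-L4 before surgery (day 0", with the second estimation at POD30, which is day 44. In Table 3 the row "Sarcopenia (Psoas area on CT scan" carries four marks: D0, D16 (POD2), D24 (POD10) and D44 (POD30). Data collection and follow up, just after Figure 1, says of the "radiological investigations performed preoperatively and then on POD2, POD10 and POD30, the assessment of remnant liver volumes and of sarcopenia" that one radiologist will do the reading. Earlier in the same section, the POD2 CT is justified by liver volume only, and sarcopenia is named for the preoperative nutritional evaluation and for the day-44 CT.

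**Liver volume.** Item v under Endpoints of trial specifies "4 successive volumetric helical computed tomography estimations of their liver volumes before surgery (day 0) then at POD2 (day 16), POD10 (day 24) and POD30". In Table 3 the row "Volumetric assessment of (future) remnant liver" is marked at the first consultation, D16, D24 and D44, and its D0 cell is blank.

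**Analysis.** Statistical analyses assigns continuous secondary endpoints to an independent-samples t-test and adds that a multivariate analysis, not further described, will complete the plan.

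**The concern.** A centre or reading radiologist cannot tell whether psoas area is to be measured on two scans or four. Nor can they tell whether the preoperative scan used for psoas is also the one used for volumetry. The text gives the two CT endpoints the same baseline day, and the table gives them different ones.

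For psoas area the number of readings affects the analysis. With two readings there is a single post-operative value, so a patient without the POD30 CT contributes nothing to the comparison, even though POD2 and POD10 scans are scheduled for every patient for volumetry. If the role of the intermediate readings stays open, the psoas time point could also be chosen after the data are seen. And an unadjusted t-test makes no use of the baseline area as a covariate, although every version of the schedule collects it.

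**Working it through.** **1. Is the mismatch an artefact of the PDF?** Both Table 3 rows have 13 fields (a label and 12 time columns), the same as the header, so each mark can be matched to its column.

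| Source | Psoas area | Liver volume |
|---|---|---|
| Endpoints of trial, items v and vi | D0, POD30 | D0, POD2, POD10, POD30 |
| Table 3 | D0, POD2, POD10, POD30 | First consultation, POD2, POD10, POD30 |
| Single-radiologist sentence | Preoperative, POD2, POD10, POD30 (named jointly with liver volume) | Same |
| Text on POD2 and day-44 CTs | Day 44; POD2 tied to liver volume only | POD2, day 44 |

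The psoas count differs by 4 − 2 = 2 readings, POD2 and POD10. For liver volume the count agrees, and only the baseline day differs.

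**2. What baseline adjustment gains over a t-test.** Take equal variance (set to 1) at each visit and a baseline-to-POD30 correlation ρ₀, which the article does not give. The variance per patient is 1 for the POD30 value alone, 2(1 − ρ₀) for the change, and 1 − ρ₀² after adjustment for baseline.

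| ρ₀ (assumed) | POD30 value | Change | Adjusted | Value / adjusted | Change / adjusted |
|---|---|---|---|---|---|
| 0.5 | 1 | 1.00 | 0.75 | 1.33 | 1.33 |
| 0.7 | 1 | 0.60 | 0.51 | 1.96 | 1.18 |
| 0.9 | 1 | 0.20 | 0.19 | 5.26 | 1.05 |

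The article does not say whether the t-test is on the POD30 value or on the change. Under these assumptions the adjusted model is more precise in both cases.

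**3. What POD2 and POD10 add.** Let m be the fraction without a POD30 scan, with POD2 and POD10 observed. Compare a baseline-adjusted analysis of complete cases with a likelihood model using all scans. The variances are proportional to 1/(1 − m) and to R² + (1 − R²)/(1 − m), so their ratio is 1/(1 − m·R²). Here R² is the share of POD30 variance, given baseline, that POD2 and POD10 explain.

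Assume a correlation of 0.90 between baseline and every later scan, and ρ among the post-operative scans. The partial correlation is r = (ρ − 0.81)/0.19, and R² = 2r²/(1 + r).

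| ρ | r | R² | m | Variance ratio |
|---|---|---|---|---|
| 0.92 | 0.579 | 0.425 | 10% | 1.04 |
| 0.95 | 0.737 | 0.625 | 10% | 1.07 |
| 0.97 | 0.842 | 0.770 | 10% | 1.08 |
| 0.96 | 0.789 | 0.697 | 5% | 1.04 |
| 0.96 | 0.789 | 0.697 | 10% | 1.07 |
| 0.96 | 0.789 | 0.697 | 20% | 1.16 |

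The range 1.04 to 1.08 is about 2 to 4% in standard error (√1.04 = 1.02, √1.08 = 1.04). Whatever the correlations, the ratio lies between 1 (R² = 0) and 1/(1 − m) (R² = 1), which is 1.11 at 10% and 1.25 at 20%.

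**4. Deaths.** Background cites about 3.5% 30-day mortality after liver resection. Applied to 400 patients this is 0.035 × 400 = 14. For such patients a POD30 psoas area does not exist, so they are not part of m.

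**The case against.** The two-scan version has support. Item vi and the text on the POD2 and day-44 CTs agree with each other, and the single-radiologist sentence may only list all scans and both measures without fixing which measure is read on which scan. A baseline-to-POD30 endpoint is legitimate even when intermediate values are collected. This stands: the article does not settle whether two or four is intended.

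Several stronger inferences are tempting, and the article does not support them:

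- *The plan discards two readings.* No passage excludes the POD2 or POD10 values from analysis. Item vi simply does not mention them.
- *The volumetry baseline biases an endpoint.* It has no bearing on psoas area. Both candidate days precede the supplement, the regeneration formula is not shown, and POD2 is the scan said to establish remnant volume. It is a timing inconsistency with no demonstrated effect.
- *The 10% drop-out means 40 patients lose their POD30 scan.* That allowance is attributed to non-compliance, intolerance and the like, and the article plans a day-44 CT for all patients. In the working, 10% is an illustration only.
- *A repeated-measures model repairs loss through death or complications.* The calculation concerns precision, not bias. The model assumes missingness at random given the observed scans, and it would imply POD30 values for patients who died.

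It can also be said that the choice of model belongs to an analysis plan that is not shown. But the article itself names the t-test, and the undescribed multivariate analysis does not replace it. Finally, nothing shows that psoas area at POD2 measures the same thing as at POD30. This is a reason to keep POD30 as the reported contrast and to use the earlier readings only as supporting repeated measures.

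**Conclusion.** Both contradictions are in the current text: two against four psoas readings, and day 0 against first consultation for baseline volumetry. They are separate and concern secondary endpoints only. The sample size rests on complication rates of 36% and 24% and has no psoas input, so the primary endpoint, alpha, power and N do not change.

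A cheap improvement goes with the reconciliation. Adjustment for baseline psoas area is preferable to the unadjusted t-test. The further gain from POD2 and POD10 is modest, and it depends on correlations that the article does not give, on the assumed fraction of missing POD30 scans, and on missingness at random among survivors. This is a minor point, worth acting on because the scans are already planned.

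**What to change.** 1. Reconcile items v and vi under Endpoints of trial, the psoas and liver-volume rows of Table 3, and the two places in Data collection and follow up that describe the CTs and their reading. State how many psoas readings count, and which existing preoperative scan is the baseline for each CT endpoint. If four psoas readings are intended, item vi changes and the description of the CTs should say so. If two, the Table 3 row and the single-radiologist sentence change.
2. Keep the POD30 difference between arms as the reported psoas contrast, fixed before the data are seen.
3. Replace the t-test for this endpoint with a model adjusted for baseline psoas area. Where POD2 and POD10 are read, include them as repeated measures in a likelihood-based mixed model, so that surviving patients who miss the POD30 CT still contribute.
4. Report deaths before POD30 separately by arm, and say that the psoas contrast concerns patients alive at POD30.

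The cost is endpoint and table wording, one model, and two more psoas contours per patient (at most 2 × 400 = 800) for the radiologist already assigned to those scans. No additional CT is needed.
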